### Parent study

The Genomic Cancer Medicine Program includes a large cohort study funded by the NSW Ministry of Health, Australia, the Molecular Screening and Therapeutics (MoST) Program. MoST is recruiting 1000 adult patients with pathologically confirmed advanced or metastatic solid cancer with a particular focus on rare or neglected cancers. Participants undergo TGP, and receive results at approximately 11 weeks. Their treating oncologist is informed of results and discusses results and treatment options with the patient. Possible treatment options identified through TGP include a clinical trial offered as part of the MoST program, another clinical trial available in Australia, or off-label treatment through the treating clinician. This cohort offers the opportunity to explore short- and long-term impacts on behaviour and psychological morbidity of receiving TGP results. The PiGeOn project constitutes a psycho-social/ethical sub-study in this cohort, employing mixed methods to gather patient-reported outcomes and qualitative data.

### Research design

This is a mixed method, prospective, cohort sub-study of a TGP programme enrolling patients with advanced cancer.

### Setting

Participants will be recruited by the parent programme, from incident and prevalent cases at three large tertiary oncology units in Sydney hospitals. All suitable participants will provide informed consent using established procedures for genetic research, validated by large genetic studies. [13, 14] The scope of this consent includes TGP as well as completion of questionnaires and interviews. Participants are provided with actionable and non-actionable results from TGP and they can elect whether they want germline genetic results confirmed by Sanger sequencing and returned. Patients for whom germline variants are found will have their decision to be informed confirmed, then directed to a genetic counsellor for further information.

### Participants

The target population includes patients with pathologically confirmed advanced or metastatic solid cancer of any histologic type. Patients with rare or neglected cancers (defined as an incidence of less than 6/100,000 of the general population and cancers of unknown primary site) will be given priority.

*Inclusion criteria* include: age 18 years or older; pathologically confirmed advanced and/or metastatic solid cancer or an earlier diagnosis of a poor prognosis cancer; sufficient and accessible tissue for TGP; failed all standard anticancer therapy or receiving last line of standard therapy at time or enrolment; Eastern Cooperative Oncology Group Performance Status Measure (ECOG) performance status 0, 1 or 2; willing and able to comply with all study requirements, including timing and/or nature of required assessments; and written informed consent.

*Exclusion criteria* include: suitability for standard therapy, if the patient has not been previously treated; specific co-morbidities or conditions which may contraindicate participation or compromise assessment of key outcomes; history of another malignancy within 2 years prior to registration: pregnancy, lactation or inadequate contraception.

### Procedure for PiGeOn

Patients will provide consent to MoST staff for the psychosocial (PiGeOn) sub-study at the same time as they give consent to the parent TPG program. Thus at baseline they will have already considered and given consent to TGP, but not yet had TGP. Participants will be asked to complete a questionnaire (hard copy, online or via telephone if they prefer) at baseline (T0), 1 to 4 weeks after receiving TGP results (T1, approximately 2–3 months post baseline), and at 2 months (T2) after T1. These timeframes have been chosen to allow impacts of the test results to be captured in both the short-term (when a treatment decision is being made) and longer-term (while undergoing or near to completion of targeted therapy, if adopted). A small subset (around 20–40 participants) will be invited to participate in semi-structured interviews at the same assessment time points to explore in more detail attitudes towards TPG and its associated psycho-social, behavioural and ethical aspects. See Fig. 1.

**Fig. 1 Fig1:**
[figure not shown]
Assessment schedule. MoST PS: MoST Psychosocial (PiGeOn) sub-study

### Measures

The following patient-reported measures will be collected (see Table 1).

**Table 1 Tab1:** Survey measures

Domain	Measures	Baseline (T0)	Follow-up 1 (T1) (within 4 weeks of return of results, ~ 2–3 months)	Follow-up 2 (T2) (2 months post T1)
Demographics				
Age, gender, marital status, education level, occupation etc	Demographic items	X		
Views and attitudes				
Value of TGP	Adapted from previous studies [15–17]	X		
Perceived benefits and drawbacks of TGP	Adapted from Jamal et al. [18]	X	X	
Result return preferences	Adapted from Tabor et al. [19]	X		
Knowledge	Study-developed	X		
Perceived importance of TGP	Adapted from Hay et al. [20]	X		
Psychological predictors				
Coping with uncertainty	Kasparian et al. [21]	X		
Self-efficacy	Adapted from Rosenberg et al. [22]	X		
Perceived susceptibility	Adapted from Kasparian et al. [21]	X	X	X
Psychological outcomes				
Coping with TGP results	Multidimensional impact of cancer risk assessment [23]		X	
Fear of cancer progression	Concerns about Recurrence Questionnaire [24]	X	X	X
Cancer -specific anxiety	Impact of events scale [25]		X	X
Anxiety and depression	Hospital anxiety and depression scale [26]		X	X
Hope	Herth Hope Index [27]		X	X
Decisional outcomes				
Decisional conflict	Decisional conflict scale [28]		X	
Decisional regret regarding personalised treatment	Decision regret scale [29]			X
Decisional satisfaction	Satisfaction with Decision Scale [30]	X	X	

TGP, Tumour genomic profiling

### Demographic data

Age, gender, marital status, education level, occupation, language spoken at home and history of genetic screening collected by patient report at baseline. Sociodemographic status will be derived from National Census data based on location of residence.

### Disease details

Available from the MoST database, including family history, primary site, detailed staging, ECOG performance status, treatment and co-morbidities.

The following validated (some adapted) outcome measures will be administered at baseline only:

### Perceived importance of TGP

This 2-item measure adapted from Hay et al. [15] assesses perceived importance of genetic information to the participant, using a Likert scale. Specifically, the questions pertain to importance of learning about how genes affect the chance of responding to particular cancer treatment, and how lifestyle affects the chance of living longer with cancer. High scores indicate greater importance.

### Knowledge

A 9-item, multiple choice, study-developed questionnaire assessing knowledge of the purpose of TGP, likely frequency of informative results, cancers in which informative results are more likely to be found, availability of tailored treatment options, and source of genetic knowledge. Scores are summed, with high scores indicating greater knowledge.

### Self-efficacy

Four items adapted from Rosenberg et al., [16] assessing perceived ability to cope if actionable, non-actionable, or germline results are found. High scores indicate greater perceived ability to cope.

### Value of TGP

A hypothetical time trade-off scenario based on those used in three previous studies. [17–19] Six items assess how the likelihood of finding an informative result impacts willingness to have TGP, and the amount the participant would be willing pay for TGP (from $0 to $10,000) if TGP found an informative result in 1, 20, or 40 people out of 100.

### Preferences for being informed of results

Four Likert-scale items adapted from Tabor et al., [20] assessing desire for results informing: treatment, prognosis, and family risk of cancer (yes / no / maybe / don’t know).

### Coping with uncertainty

Eight Likert-scale items from Kasparian et al., [21] measuring reaction to uncertainty, ambiguity and the future. High scores indicate greater intolerance.

Note that to reduce participant burden at baseline, measures of psychological morbidity (anxiety, depression, hope) were not included at T0.

The following outcome measures will be administered at the first follow-up only:

### Coping with genetic test results

The 25-item Multidimensional Impact of Cancer Risk Assessment [22] assessing impact of result disclosure after genetic testing. High scores indicate greater distress.

### Decisional conflict regarding tailored treatment

Ten items from the Decisional Conflict Scale [23] comprises 5 subscales measuring: 1) uncertainty, 2) feelings of being uninformed, 3) clarity of values, 4) sense of being unsupported in decision-making, and 5) evaluation of the quality of the decision. High scores indicate lower decisional conflict.

The following outcome measures will be administered at the first and second follow-ups:

### Cancer-related anxiety

The 15-item Impact of Events Scale [24] assesses cancer-related anxiety, in two subscales, intrusive thinking and avoidance. High scores indicate greater cancer-related anxiety.

### Anxiety and depression

The 14-item Hospital Anxiety and Depression Scale [25] comprises two 7-item sub-scales measuring anxiety and depression. High scores indicate greater morbidity.

### Hope

The 12-item Herth Hope Index [26] measures hope and sense of meaning, with 3 subscales: temporality and future, positive readiness and expectancy, and inter-connectedness. High scores indicate greater hope.

The following outcome measure will be administered at the second follow-up:

### Decisional regret

The 5-item Decisional Regret Scale [27] measures health care decision regret about the decision to have TGP. High scores indicate greater regret.

The following outcome measures will be administered at baseline and first follow-up:

### Perceived benefits and drawbacks of TGP

Two open ended questions adapted from an earlier study [28] assessing perceived specific benefits and drawbacks of TGP.

### Satisfaction with decision to have TGP

The 6-item Satisfaction with Decision scale [29] measures satisfaction with decision to have TGP. Items are rated on a Likert scale. High scores indicate greater satisfaction.

The following outcome measures will be administered at baseline and all follow-ups:

### Fear of cancer progression

Three items from the Concerns about Recurrence Questionnaire [30], adapted to measure fear of cancer progression. High scores indicate greater fear.

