## Methods/design

### Aims and hypotheses

The aim of this study in adults with advanced cancer undergoing TGP is to:*Before and after receipt of results:* evaluate knowledge of TGP, preferences for genetic information, attitudes (positive and negative) and the value placed on TGP;*After receipt of results:* identify behavioural, decisional and psychological outcomes from TGP along with their respective predictors; andContextualize the findings via a critical bioethics analysis.

Specific hypotheses are that:At baseline (after giving informed consent to undergo TGP), advanced cancer patients will have moderate to poor knowledge about TGP (< 55% correct on knowledge scale).At baseline, advanced cancer patients will have primarily positive attitudes to, and highly value, TGP.Of advanced cancer patients *who receive an actionable result*, most will:Pursue personalised treatment in a clinical trial setting (behavioural outcomes).Cope well with results, and experience low decisional conflict and regret and high decisional satisfaction (decisional outcomes).Have higher hope, less cancer-related anxiety, lower fear of cancer progression and lower general anxiety and depression than those who do not receive actionable results (psychosocial outcomes).Those advanced cancer patients who have *no actionable variants identified* will:Struggle to cope with non-results (decisional outcomes).Have levels of hope, cancer-related anxiety, fear of cancer progression and general anxiety and depression similar to published results for advanced cancer patients who have not undergone TGP, within 1 month of receiving results and 5 months later (psychosocial outcomes).5.Predictors of behavioural, decisional and psychological outcomes within 1 month of receiving results and 5 months later, will include:Age, education level, ethnicity, and gender;Tolerance of uncertainty and baseline knowledge; andPreferences and attitudes to TGP.

Methodology in critical bioethics analysis is not hypothesis-driven and to this end there are no hypotheses relating to this part of the analysis.

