### Quantitative data analysis

Mean differences in outcomes will be compared using t-test (continuous) or chi-squared tests (dichotomous). Non-parametric tests will also be used where appropriate. Temporal changes in scales will be investigated by calculating the difference between time-points. Multiple (continuous outcomes) or logistic (dichotomous outcomes) regression will be used to adjust for the effect of confounders and identify predictors of outcome. Linear mixed models and logistic mixed models will be carried out in R: A language and environment for statistical computing using package nlme for the linear mixed model and lme4 for the logistic mixed model. Assumptions of normality of residuals and homogeneity of variance will be checked visually though diagnostic residual plots. Multivariable models will be constructed with the inclusion of all potential confounders, and those predictors that show weak evidence for an association with the outcome in univariate analysis. Backwards elimination followed by forwards addition will be used to select predicting variables in the final model. Known and identified confounders will be included regardless of their statistical significance. Collinear independent variables will be identified and removed.

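### Fear of cancer progression after a non-actionable result is judged against published levels although it is measured with adapted items, and the hypothesis is not tied to the pre-result baseline that exists for this scale

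*Protocol article*

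**What the plan says.** Under Aims and hypotheses, the fourth hypothesis concerns patients in whom no actionable variant is found. Its psychosocial part says that they will "Have levels of hope, cancer-related anxiety, fear of cancer progression and general anxiety and depression similar to published results for advanced cancer patients" without tumour genomic profiling (TGP). The comparator is thus an external level, and it applies to fear of progression as to the other scales.

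The section Fear of cancer progression gives the instrument: "Three items from the Concerns about Recurrence Questionnaire [30], adapted to measure fear of cancer progression".

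On timing, the lead-in to that section reads "The following outcome measures will be administered at baseline and all follow-ups", and Table 1 marks the scale at T0, T1 and T2. For the other psychosocial outcomes of the hypothesis, the note under Coping with uncertainty says that "measures of psychological morbidity (anxiety, depression, hope) were not included at T0". Table 1 likewise shows no T0 mark for the Impact of Events Scale.

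Procedure for PiGeOn fixes what T0 represents: "at baseline they will have already considered and given consent to TGP, but not yet had TGP".

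Quantitative data analysis says that "Temporal changes in scales will be investigated by calculating the difference between time-points". It names no scale or hypothesis for this.

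**The concern.** A comparison with an external level is interpretable only if both sides are measured on the same scale. Here the study uses three items drawn from a recurrence questionnaire and changed to ask about progression. Published scores on the source questionnaire would concern a different question. A gap between the study mean and a published mean would then combine three things: any effect of the result, the difference in instrument, and the difference in population. The instrument part could create a gap or hide one.

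Population differences affect every scale in this hypothesis. The instrument problem is particular to this one, and this is also the one scale for which the study holds a value on identical items in the same patients before results. At stake is whether the study can say if a non-actionable result leaves fear of progression materially unchanged.

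**Working it through.** The article gives no SD, margin or power for fear of progression, so there is no stated figure to reproduce for this point. The detectable changes under Sample size are for the Impact of Events Scale.

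**Which psychosocial outcomes of the fourth hypothesis have a pre-result value (Table 1)**

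| Outcome | T0 | T1 | T2 |
|---|---|---|---|
| Fear of progression (adapted items) | yes | yes | yes |
| Impact of Events Scale | no | yes | yes |
| Hospital Anxiety and Depression Scale | no | yes | yes |
| Herth Hope Index | no | yes | yes |

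**Number of patients.** Sample size gives 469 patients at fewest and assumes 15% actionable: 469 × 0.15 ≈ 70, leaving 399 non-actionable. I take 469 as stated, although the step to it is not shown (1000 × 0.75 is 750). The Discussion expects 5–10% actionable, which leaves 446 or 422.

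**What the paired T0-T1 contrast can show.** Two-sided 5% level (sidedness assumed), 90% power:

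- Normal approximation: (1.960 + 1.282)/√399 = 3.242/19.97 = 0.162 SD of the change score. The noncentral t gives 0.163.
- With 422 or 446 patients: 0.158 or 0.154.
- In cross-sectional SD units, multiply by √(2(1 − r)), where r is the T0-T1 correlation. The article does not give r, so a range is assumed:
  - r = 0.3: 0.163 × 1.183 = 0.19 SD
  - r = 0.5: 0.163 × 1.000 = 0.16 SD
  - r = 0.7: 0.163 × 0.775 = 0.13 SD
- 95% half-width at r = 0.5: 1.96/√399 = 0.098 SD.

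A constant instrument shift is present at both time points and cancels in the difference.

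**What an instrument shift could do to the external comparison.** The article gives no size for such a shift, so these sizes are assumptions. Suppose the true difference is zero and the instrument alone moves the mean by b SD. The chance that a two-sided 5% test declares a difference in the direction of the shift is:

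| b (assumed) | Published mean treated as fixed, noncentrality b√399 | Published sample of 200 (assumed), noncentrality b/√(1/399 + 1/200) |
|---|---|---|
| 0.10 SD | 2.00, probability 0.51 | 1.15, probability 0.21 |
| 0.20 SD | 3.99, probability 0.98 | 2.31, probability 0.63 |

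**What T0 adds to the actionable versus non-actionable contrast.** With the T0 score as covariate, the residual SD is multiplied by about √(1 − r²): 0.95, 0.87 or 0.71 for r = 0.3, 0.5 or 0.7. It also adjusts for differences in fear between the groups before results.

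**The case against.** The strongest reply is that the T0 data are already in the plan. Quantitative data analysis provides for differences between time points, mixed models and confounder adjustment by regression, so change in this scale will probably be reported. That stands. A reader might infer that the baseline is collected and left unused, and the article does not support this. What remains is that the hypothesis is worded around an external level, and that the T0 score is not named as a covariate.

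Second, change from T0 answers a different question. The hypothesis asks whether these patients resemble others who had no TGP. T0 follows consent to TGP, so it may already carry the anticipation of testing. The patients are on or beyond their last standard therapy, so change over the following months also carries disease course and attrition. This stands too, and it is why the published comparison need not be deleted.

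Third, the article does not say who adapted the items or which published results will be used, and a condensed article may leave the reference data to a fuller document. A reader might infer that the study team wrote the adaptation and that no suitable norms exist. The first is the natural reading but is not stated, and the second cannot be known from the article. Reference values on the identical items would largely remove the instrument problem.

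**Conclusion.** The point holds in a limited form. As worded, the fourth hypothesis tests fear of progression against a reference that may not share its instrument, although a reference on identical items is available within the study. The paired contrast is precise enough to be useful: about 0.16 SD of the change score at 90% power, or 0.13–0.19 cross-sectional SD for assumed correlations of 0.7 down to 0.3. These figures rest on 399 non-actionable patients with paired data.

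A reader might conclude that a modest instrument shift would by itself decide the external comparison. The figures do not support that at 0.10 SD, where the probability of a spurious difference is about 0.2 to 0.5. At 0.20 SD it is about 0.6 to 0.98. All these shifts are assumed, so the finding is an avoidable ambiguity and not a demonstrated bias of known size.

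The reach is one psychological scale in one hypothesis. The primary outcomes named in the abstract (knowledge, preferences, attitudes and values) are unaffected. The change is worth making because it needs only data already being collected.

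**What to change.** 1. For fear of progression, restate the fourth hypothesis as no material within-patient change after a non-actionable result. Make the T0-T1 and T0-T2 changes in these patients the main test, each with a confidence interval, since a non-significant test alone would not show similarity.
2. In the third hypothesis, compare actionable with non-actionable patients on this scale by regression with the T0 score as covariate.
3. Keep a published comparison for this scale as descriptive context only. If reference values on the same adapted items exist, cite them, and the comparison can then carry more weight.
4. State the limit alongside the result: change from T0 also reflects disease course and attrition and starts after consent to TGP, so it speaks to the effect of the result and not to a contrast with patients who had no TGP.

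The cost is rewording part of one hypothesis and specifying two analyses. No new patients, visits or items are needed. The price in content is that, for this scale, the external question becomes descriptive.

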### Perceived susceptibility

Participants indicate perceived likelihood of having a gene fault that increases risk of cancer progression on a visual analogue scale (0–100%) adapted from Kasparian et al. [21]

### Qualitative interviews

A subset of participants will be invited to participate in three semi-structured interviews (at baseline and each follow-up). Recruitment will continue until saturation is reached. [31] As the majority of this sample population is expected to have non-actionable results, additional participants, purposively sampled to include those who have received actionable or incidental findings, will be recruited at follow-up 1 and re-interviewed at follow-up 2. Similarly, purposive sampling will be used to ensure that both patients who elect to receive, and not receive, germline results (if available) will be included. Also, the opportunity to contrast TGP with the experience of having previously undergone testing for a single variant to personalize treatment will be taken where possible. Interviews will explore views on who should be offered TGP, attitudes to disclosure of results, perceived benefits and challenges of TGP, ethical aspects of TPG testing and experiences of receiving informative and uninformative results.

### Sample size

The MoST study plans to recruit 1000 patients over three years. Thus, with a conservative retention and survival estimate of 75%, this is reduced to at fewest 469 patients. With this sample size estimate, assuming 15% of patients receive an actionable result and using a significance level of 0.05, this project: has 90% power to detect a mean change of 5.8 and 2.6 points on the Impact of Events scale for patients with actionable and non-actionable results respectively (paired t-test, SD = 15) [32] and a mean difference of 4.5 points between patients with actionable and non-actionable results; Multiple regression with at most 24 explanatory variables (including dummy variables) has 90% power to detect significant categorical variables with 5 categories (largest possible categorical variable) when that predictor explains greater than 3.6% of the residual variance, or to detect a continuous variable when it explains more than 2.3% of the residual variance. For patients with actionable results only (at fewest 70), at 80% power the minimum variance explained for continuous variables would be 12% of the residual variance, and 15% for binary predictors. For logistic regression when outcomes are on average equally likely the power to detect an odds ratio of 1.4 is 95% or 80% when the other covariates explain zero, or 37% of the outcome variance respectively. For only those with actionable results, there is 80% power to detect an odds ratio of 2.14 or greater if the other outcomes explain zero outcome variance.

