## Discussion

The PiGeOn study advances the field by identifying the knowledge, values, attitudes and coping strategies of patients with regards to TGP, determining how these, and other factors, predict subsequent cancer-related behaviour and psychosocial outcomes, and aligning these with current ethical norms. It will be the first Australian study to collect longitudinal data on cancer patients’ experience of TGP over time.

The trial experience of the first 100 patients revealed the unexpected finding that a significant proportion of the cohort was eligible for both this sub-study, and the twin psychosocial sub-study, which involved participants undergoing GGS. This group will be treated as a separate cohort, as they will be facing the combined challenges of uncertainty related to prognosis/treatment related outcomes of the MoST component, as well as the germline implications for identifying increased cancer risk for blood relatives. Previous research using hypothetical scenarios unsurprisingly suggests that patients with cancer have greater concerns about GGS than TGP. [5] This study will provide the opportunity to explore attitudes of patients who have elected to undergo both.

Methodological issues considered in the development of this study included the timing of the psychosocial assessments, including questionnaires. Timing was crucial in order to capture participant experiences and this was modified early based on data collected in the initial phase of the programme. Given it is expected that 5–10% of the cohort will have actionable somatic mutations, sampling for the qualitative component will be manipulated between baseline and follow-up 1 to allow for exploration of the reaction to both return and non-return of actionable results. The follow-up 1 cohort will be reassessed qualitatively at the subsequent follow-ups. It is recognized that there may be challenges in maintaining the follow-up of patients not receiving actionable results, although cancer populations are known to be highly motivated to contribute to research. [35] It will be important to capture the experience of having hopes of finding a novel cure raised in 100% of poor prognosis patients only to have them dashed in the at least 90% in whom nothing is found. [36]

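### The stated inputs (1000 patients, 75% retention and survival) give 750 and not 469; the missing factor is not stated, nor is whether the dual-eligible cohort is inside the 469

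*Protocol article*

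**What the plan says.** The Sample size section of the protocol article opens with the parent recruitment target: "The MoST study plans to recruit 1000 patients over three years". It then applies one reduction: "with a conservative retention and survival estimate of 75%, this is reduced to at fewest 469 patients". No uptake rate, questionnaire return rate or second attrition step is given.

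The power statements follow directly, "assuming 15% of patients receive an actionable result and using a significance level of 0.05". The study "has 90% power to detect a mean change of 5.8 and 2.6 points on the Impact of Events scale"; the first value belongs to the group with an actionable result and the second to the group without one. The test and spread behind both values are given as "paired t-test, SD = 15". The section also quotes a between-group difference of 4.5 points, detectable partial variances for multiple regression, and power for an odds ratio of 1.4 in logistic regression. The actionable subgroup is put at no fewer than 70.

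Two other places bear on the N. Setting says that consent is joint: "The scope of this consent includes TGP as well as completion of questionnaires and interviews". The Discussion reports that, in the first 100 patients, "a significant proportion of the cohort was eligible for both this sub-study" and the twin germline sub-study, and adds: "This group will be treated as a separate cohort". The size of that group is not given, and the Sample size section does not mention it.

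**The concern.** The article chose to show how the analysable N is reached, and the derivation shown does not produce the number printed. This goes beyond the condensation expected of a journal article. The figure is presented as a floor, and it is carried forward: the 70 patients with actionable results are 15% of 469. If the starting number cannot be traced, a reader cannot tell which set of detectable effects describes the study.

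The separate cohort adds to the doubt. If those patients are analysed apart from the main cohort and are still counted in the 469, the main analyses would have fewer patients than the stated minimum. If they have already been taken out, the minimum may stand. The text does not let the reader decide.

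**Working it through.** **Inputs.** From Sample size: 1000 recruits, 75% retention and survival, stated N 469, 15% actionable, alpha 0.05, SD 15, 90% power. Alpha is taken as two-sided, which the article does not say. The 15% is taken as given; the Discussion's 5–10% expectation is a separate matter.

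**Step 1: reproduce 469.**
- 75% once: 1000 × 0.75 = 750
- 75% twice: 1000 × 0.75² = 562.5
- 75% three times: 1000 × 0.75³ = 421.9
- Back-calculation: 469 / 0.75 = 625.3, and 625 × 0.75 = 468.75
- Missing factor: 469 / 750 = 0.625, a further loss of about 37.5%, or 750 − 469 = 281 patients

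No repetition of the stated 75% gives 469.

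**Step 2: which quoted figures fit 469?** The split is 0.15 × 469 = 70 actionable and 399 non-actionable. The multiplier is (1.960 + 1.282) × 15 = 48.62.
- Paired change: 48.62 / √n. For n = 70 this is 5.81 (5.89 with the t distribution). For n = 399 it is 2.43 (2.44 with t).
- Between groups: 48.62 × √(1/70 + 1/399) = 48.62 × 0.1296 = 6.30 (6.31 with t).
- Power for 4.5 points: 4.5 / (15 × 0.1296) = 2.315; 2.315 − 1.960 = 0.355; Φ(0.355) ≈ 0.64.
- Logistic, odds ratio 1.4, outcomes equally likely (taken as per SD of a continuous predictor): ln 1.4 × √(469 × 0.25) = 3.64; 3.64 − 1.96 = 1.68; power 95.4%. With 37% of variance explained by other covariates: 3.64 × √0.63 = 2.89; power 82.4%.
- Partial variance with 24 predictors, noncentral F: 2.2–2.3% for a continuous predictor and 3.2–3.5% for a five-category one. The range reflects the convention used for the noncentrality parameter.

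| Quantity | Stated | At N = 469 |
|---|---|---|
| Actionable patients | 70 | 70 |
| Paired change, actionable | 5.8 | 5.8–5.9 |
| Paired change, non-actionable | 2.6 | 2.4 |
| Between-group difference | 4.5 | 6.3 |
| Continuous predictor | 2.3% | 2.2–2.3% |
| Five-category predictor | 3.6% | 3.2–3.5% |
| OR 1.4, no other variance explained | 95% | 95.4% |
| OR 1.4, 37% explained | 80% | 82.4% |

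So 469 was used for part of the paragraph and does not explain all of it. The 2.6 corresponds to about 352 non-actionable patients and not 399. The 4.5 needs (48.62 / 4.5)² / (0.15 × 0.85) ≈ 916 patients in total for 90% power.

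**Step 3: the same quantities at 750** (112 actionable, 638 non-actionable). Paired changes are 4.6 and 1.9 points and the between-group difference is 5.0. An odds ratio of 1.4 has 99.6% power, or 95.5% with 37% explained. The 4.5-point difference has 83% power, so it does not reach 90% here either.

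**Step 4: the dual-eligible group.** Its share is not given, so the shares below are assumptions.

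| Assumed share removed | From 750 | From 469 | Between-group difference at the lower N |
|---|---|---|---|
| 10% | 675 | 422 | 6.7 |
| 20% | 600 | 375 | 7.1 |
| 30% | 525 | 328 | 7.6 |

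Starting from 750, the total falls below 469 only if more than 37.5% are removed. The columns based on 469 apply only if the group is still counted in that number.

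**The case against.** The strongest reply is that 469 is a cautious planning number with a step left out of the text. Joint consent does not mean that everyone returns a questionnaire: patients are only asked to complete them, and in advanced cancer some will not return the baseline form or reach the first follow-up. Other chains also reach the number. For example, 75% at each of the two follow-ups with recruitment at five sixths of target gives 1000 × 5/6 × 0.75 × 0.75 = 468.75. That chain is not in the article, but it shows that a single hidden loss of 37.5% is not the only explanation. Since 469 is below 750, the proven discrepancy does not by itself show any loss of power. All of this stands, and it limits the point to an untraceable N.

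Three stronger readings are tempting, and the documents do not support them.

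- A reader might infer that the 469 fails to deduct the dual-eligible patients. The derivation is not shown, so the unexplained 281 could include them. Only the absence of a stated deduction can be asserted. For the same reason, subtracting an assumed share from 469 may count one loss twice.
- A reader might infer that every power figure rests on 469. Step 2 shows otherwise: the 4.5-point and 2.6-point figures do not come from it.
- A reader might infer that 469 should simply become 750. That would assume full questionnaire participation and replace the smaller N without evidence that the smaller one is wrong.

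The reply does not supply the missing step. The sentence as printed still gives 750.

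**Conclusion.** The point holds as an arithmetic and reporting fault. The stated inputs yield 750, the text says 469, and nothing in the article accounts for the factor of about 0.625 between them. The description of 469 as a minimum is unsupported, because the chain to it is undisclosed and a planned separate cohort of unknown size is neither included nor excluded explicitly.

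The direction is open. On the stated inputs alone the planning N is conservative by 281 patients. It becomes optimistic only if true losses, including the separate cohort where it is analysed apart, exceed those already built into 469. The article gives no figure from which to judge that.

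Settling the N will not by itself repair the paragraph. At 469 the between-group detectable difference is 6.3 points and not 4.5, a material overstatement of sensitivity. The non-actionable paired change is 2.4 and not 2.6, an error in the cautious direction. These results assume two-sided alpha 0.05, SD 15 for both the change and the between-group comparison, and the 15:85 split.

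**What to change.** In the Sample size section:

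1. Write out the chain from 1000 recruits to the analysed N, naming each factor (for instance uptake, questionnaire return, survival, retention to each follow-up). If no factor beyond the 75% exists, correct the N.
2. State whether the dual-eligible patients are inside or outside that N, and give their observed or expected share. Keep the description of 469 as a minimum only if the chain supports it.
3. Recompute all detectable effects from that single N, including the between-group difference and the non-actionable paired change, and state the sidedness of the tests.

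The cost is rewording and recalculation. Recruitment, questionnaires and analysis methods do not change.
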